**Discussion:**

We hypothesise that the benchmarking intervention can improve the adoption of health-enabling store policy and practice and reduce sales of unhealthy foods and drinks in remote community stores of Australia. This innovative research with remote Aboriginal and Torres Strait Islander communities can inform effective implementation strategies for healthy food retail more broadly.

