#### Outcomes

Primary outcome: Change in the last six-months (July-December 2023) from baseline (July-December 2021) in free sugars from all food and drinks purchased (g sugar/MJ total energy), derived from electronic point-of-sale data.

Secondary outcomes: Change from baseline to i) last six months of 2022 and ii) last six-months of 2023 for the following purchasing outcomes derived from data of all food and drinks purchased:free sugars (g/MJ total energy)discretionary products weight (g/MJ total energy)core products weight purchased (g/MJ total energy)sodium (mg/MJ total energy)

Change from baseline (2022) in 2023 and 2024 in adoption of best-practice store policy action and practice implementation.

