#### Participant timeline

For intervention stores, the benchmarking cycle involves an assessment in July/August of 2022, 2023 and 2024. Feedback reports are then provided to partners for store groups and independent stores directly between October/November of 2022, 2023 and 2024. Action plan meetings are arranged by partners with stores following receipt of feedback reports in 2022 and 2023. Store directors/owners/ management then have responsibility to implement the co-designed action plans. Action implementation occurs following action plan meetings to June of each year before assessment starts again in July/August.

For control stores, data collection occurs in July/August, 2022 (using Store Scout App) and 2023 (using Store Scout App and Healthy Diets ASAP). One full benchmarking cycle will be completed, commencing with assessment in July/August, 2024.

As shown in Table 1, weekly sales data are collected from intervention and control stores from 2021 to 2025.

**Table 1 Tab1:** Summarised benchmarking performance metrics and data collection methods

Benchmark assessment area	Stores assessed	Data collector	Data collection instrument (Supplementary material)	Estimated data collection time
i) Policy: adoption of health-enabling best-practice store policy	Intervention stores (2022, 2023, 2024) Control stores in 2024	Store owner/s (for privately owned stores), store representatives or store nutritionists for stores with ALPA or Outback Stores (and with area managers for Outback Stores)	Policy Action Progress Audit e-survey: 24 three-part item survey on adoption status (full, partial, getting started, not yet started) of 21 industry- and research-informed policy actions [62]. Survey informed by research evidence, the remote food retail, government policy and health and research sectors, and BIA-Obesity, and built in REDCap [32, 64].	~ 30 min
ii) Practice: implementation of best-practice	Intervention and control stores (2022, 2023, 2024)	Trained partner nutrition practitioners/research team	Store Scout App [65]: 293 item survey on product, placement, price promotion, and product promotion in seven food/drink categories [59].	40-60 min
iii) Price: Price of standardised healthy diet	Intervention and control stores (2023/2024 only)	Trained partner nutrition practitioners/research team	Aboriginal and Torres Strait Islander Healthy Diets ASAP: on-line survey to collect food price data on 76 healthy and unhealthy food/ drink products [61].	~ 60 min

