### Analysis and statistical methods

The data source for analysis of the primary outcome and some secondary outcomes is weekly sales reports provided by the stores. Unique store products are linked, using rule-based algorithms, machine learning and human verification, to nutrient data derived from the Australian Food, Supplement, and Nutrient Database, with discretionary food flagged from the Discretionary Food List developed by the Australian Bureau of Statistics [74, 75]. We use built-in, reliable data checking processes developed over the last decade in our research to assess and quantify the nutritional impact of sales.

Following data aggregation, the outcomes will be log-transformed. The main analysis for an outcome will be a simple ANCOVA analysis using sales data from July to December 2021 and 2023, and randomisation group for the primary outcome.

We anticipate that the impact of the intervention will be both immediate and gradual. In stores that receive the benchmarking intervention, we estimate an immediate 3.5% reduction in free sugars to energy purchased as a result of food retail practice change. A reduction in free sugars to energy at this level from the baseline shown in the Healthy Stores 2020 trial has been shown to be the equivalent to an approximate 10% lower risk for cardiovascular disease mortality [4]. We then expect a more gradual effect at the broader remote store level post-intervention as the benchmarking model is scaled up into policy and practice by different jurisdictions for the benefit of all remote communities, if found to be adoptable and effective.

Implementation fidelity will be assessed according to i) proportion of partner organisation representatives completing training; and, ii) annual benchmarking cycles fully completed in specified timeframes. Data will be collected on action plans and the resource input to their implementation.

Change in store best-practice policy action adoption and practice implementation with time will be described and used to interpret results of primary and secondary outcomes. Food price and Environment Scan survey results will be described for context.

Policy Action Assessment: Proportion of policy actions by adoption status (fully adopted, partially adopted, getting started, not yet started) for 2022, 2023 and 2024 for each intervention store will be calculated and any differences with time described.

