Practice assessment: An overall score out of 100 is derived automatically by the Store Scout App following each store assessment in 2022, 2023 and 2024 in addition to a score out of 100 for each food/drink category. Differences in total and category scores with time for intervention stores and between intervention and control stores will be described.

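### Change from 2022 in policy adoption is a secondary outcome that cannot be computed for control stores, and its stated analysis covers intervention stores only

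*Protocol article*

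**What the plan says.** The Outcomes section of the protocol article defines, among the secondary outcomes, "Change from baseline (2022) in 2023 and 2024 in adoption of best-practice store policy action and practice implementation". The hypothesis in the Abstract is causal: "We hypothesise that the benchmarking intervention can improve the adoption of health-enabling store policy and practice". The Background repeats it, and the Methods describe a randomised two-arm superiority trial.

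The measurement schedule differs between the two halves of this outcome. In Table 1 the policy audit is scheduled as "Intervention stores (2022, 2023, 2024) Control stores in 2024", whereas the practice assessment is scheduled as "Intervention and control stores (2022, 2023, 2024". The Participant timeline agrees: "For control stores, data collection occurs in July/August, 2022 (using Store Scout App) and 2023 (using Store Scout App and Healthy Diets ASAP". It adds, for the same stores, "One full benchmarking cycle will be completed, commencing with assessment in July/August, 2024".

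The planned analyses differ in the same way. In Analysis and statistical methods, the proportion of policy actions in each adoption category "for 2022, 2023 and 2024 for each intervention store will be calculated and any differences with time described". For practice the plan is: "Differences in total and category scores with time for intervention stores and between intervention and control stores will be described".

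**The concern.** A secondary outcome of a randomised trial would normally be read as a contrast between arms, and a stated hypothesis about policy adoption strengthens that reading. For policy, the control arm has neither the 2022 baseline nor the 2023 value that the definition needs, and the stated analysis does not use the one year in which both arms are audited.

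What remains is a before-after description in one arm. A rise in adopted policy actions could reflect benchmarking. It could equally reflect a general trend, a decision taken across a store group, an initiative begun independently of the trial (the protocol acknowledges that stores may start these), or respondents' growing familiarity with the survey. Nothing in the planned analysis separates these explanations.

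**Working it through.** The plan gives no computed figure for the policy outcome. Its only sample-size calculation concerns free sugars and has no bearing here. The check is therefore mainly a comparison of definition, schedule and analysis.

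**1. Which values exist, by arm and year** (Table 1 and Participant timeline)

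| Measure | Arm | 2022 | 2023 | 2024 |
|---|---|---|---|---|
| Policy audit | Intervention (15) | yes | yes | yes |
| Policy audit | Control (17) | no | no | yes |
| Practice score | Intervention (15) | yes | yes | yes |
| Practice score | Control (17) | yes | yes | yes |

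Arm sizes are from Allocation. The annual control assessment described under Intervention is an in-store assessment of practice, so it does not supply a policy baseline.

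**2. Can the defined outcome be formed?** Change needs a 2022 value and a later value.
- Policy, intervention: 15 of 15 planned, at both 2023 and 2024.
- Policy, control: 0 of 17 at 2023, because both values are missing, and 0 of 17 at 2024, because the baseline is missing.
- Practice: both arms, at both times.

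**3. What comparison is still possible for policy?** Only 2024 v 2024. Control stores open their own cycle with the July/August 2024 assessment and keep to usual practice until that cycle. In the cycle, feedback follows assessment. A control audit completed before that store's feedback is therefore unexposed to feedback and action planning, while intervention stores have been through two cycles.

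**4. How precise would it be?** Inputs: 15 and 17 stores (Allocation), and an SD of 0.15 to 0.20 for the store-level proportion of the 21 actions fully adopted. The SD is an assumption, because the article gives none.

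Standard error = SD × √(1/15 + 1/17) = 0.354 × SD.

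Half-width of the 95% interval = t(0.975, 30 df) × 0.354 × SD = 2.042 × 0.354 × SD.
- SD 0.15: 0.108, about 11 percentage points, or 0.108 × 21 = 2.3 actions.
- SD 0.20: 0.145, about 14 percentage points, or 0.145 × 21 = 3.0 actions.

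The difference detectable with 80% power (two-sided 5%, t-based) is 1.03 SD. That is 1.03 × 0.15 = 0.15 to 1.03 × 0.20 = 0.21.

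These figures treat the stores as independent and all 32 as audited. Two store pairs share a community and were allocated together, and stores within a group may share policy, so the real interval could differ.

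**The case against.** The strongest reply is that policy adoption is not meant as a randomised effect. Analysis and statistical methods says that policy and practice change over time will be described and used in interpreting the other outcomes, and it plans no test or effect estimate. This stands in part: the article does not itself state that any policy gain will be attributed to benchmarking. It does not remove the conflict, because the same measure is listed as a secondary outcome and the hypothesis names policy adoption.

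A reader might infer that the randomised comparison is lost for the whole outcome. The documents do not support that. Practice is measured in both arms every year, a between-arm description is planned, and the sales-based outcomes also cover both arms. The defect is confined to policy.

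A second reply is that an analysis plan not shown here could add a 2024 comparison. It could: the article omits that contrast but does not exclude it. No analysis plan, however, can create the missing 2022 and 2023 control values, so the outcome as defined stays unavailable for controls.

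A reader might also infer that the 2024 audit offers a clean randomised comparison waiting to be used. That goes too far, for these reasons:
- The audit is an e-survey answered by owners, store representatives or store-group nutritionists. Participating stores and partner representatives are unblinded.
- In 2024 intervention stores answer for the third time and controls for the first, so survey familiarity becomes a difference between arms.
- Randomisation was within the store group serviced by each partner. Group-level policy, or the same respondent answering for both arms, could dilute the contrast.
- The October/November feedback dates appear in the text on intervention stores. For controls only the order, assessment before feedback, is supported.
- The Intervention section says controls are offered the 2024 cycle, while the Participant timeline says it will be completed. So 15 v 17 is a maximum.

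**Conclusion.** The point holds for policy adoption only. The outcome is defined as change from 2022, but it cannot be formed for any of the 17 control stores, and the stated analysis is an uncontrolled description of intervention stores. As written, it cannot support the hypothesis that benchmarking improves policy adoption. The data schedule and the stated analysis fix this, so it is not a detail merely left unsaid.

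The weight is moderate: half of one secondary outcome, described rather than tested, with the primary and purchasing outcomes untouched. The half-width of 11 to 14 percentage points measures how precise the remedy would be, not how large the error is. It rests on the assumed SD, on independent stores and on complete 2024 audits. Such a comparison could show only a large difference, of about 15 to 21 points at 80% power under the same assumptions.

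**What to change.** 1. In Outcomes, separate policy from practice. State that the 2022-2024 change in policy adoption is a descriptive measure in intervention stores only and is not an estimate of a randomised effect.
2. Add a between-arm comparison at the 2024 audit: the proportion of the 21 actions fully adopted, and the proportion fully or partially adopted. Use only control audits completed before that store's feedback. Report the difference with a 95% interval that accounts for the randomisation stratum and for the two same-community store pairs.
3. Record who answered each 2024 audit and whether that person answered for stores in both arms. Report how many control stores completed it.
4. State the limits beside the result: no baseline adjustment; unblinded self-report with third-time against first-time respondents; possible dilution through shared store-group policy or respondents; at most 15 v 17 stores.
5. Because the trial is registered and began in 2022, date the addition, and say whether it was made before anyone saw the 2024 audit data.

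The cost is mainly outcome and analysis wording, plus a note of respondent and completion date at an audit already scheduled. No further assessment of stores is needed.

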#### Participant timeline

For intervention stores, the benchmarking cycle involves an assessment in July/August of 2022, 2023 and 2024. Feedback reports are then provided to partners for store groups and independent stores directly between October/November of 2022, 2023 and 2024. Action plan meetings are arranged by partners with stores following receipt of feedback reports in 2022 and 2023. Store directors/owners/ management then have responsibility to implement the co-designed action plans. Action implementation occurs following action plan meetings to June of each year before assessment starts again in July/August.

For control stores, data collection occurs in July/August, 2022 (using Store Scout App) and 2023 (using Store Scout App and Healthy Diets ASAP). One full benchmarking cycle will be completed, commencing with assessment in July/August, 2024.

As shown in Table 1, weekly sales data are collected from intervention and control stores from 2021 to 2025.

**Table 1 Tab1:** Summarised benchmarking performance metrics and data collection methods

Benchmark assessment area	Stores assessed	Data collector	Data collection instrument (Supplementary material)	Estimated data collection time
i) Policy: adoption of health-enabling best-practice store policy	Intervention stores (2022, 2023, 2024) Control stores in 2024	Store owner/s (for privately owned stores), store representatives or store nutritionists for stores with ALPA or Outback Stores (and with area managers for Outback Stores)	Policy Action Progress Audit e-survey: 24 three-part item survey on adoption status (full, partial, getting started, not yet started) of 21 industry- and research-informed policy actions [62]. Survey informed by research evidence, the remote food retail, government policy and health and research sectors, and BIA-Obesity, and built in REDCap [32, 64].	~ 30 min
ii) Practice: implementation of best-practice	Intervention and control stores (2022, 2023, 2024)	Trained partner nutrition practitioners/research team	Store Scout App [65]: 293 item survey on product, placement, price promotion, and product promotion in seven food/drink categories [59].	40-60 min
iii) Price: Price of standardised healthy diet	Intervention and control stores (2023/2024 only)	Trained partner nutrition practitioners/research team	Aboriginal and Torres Strait Islander Healthy Diets ASAP: on-line survey to collect food price data on 76 healthy and unhealthy food/ drink products [61].	~ 60 min
iv) Purchasing: Healthiness of customer purchasing	Intervention and control stores (2021–2025)	Trained partner nutrition practitioners/research team	Weekly sales data provided by store businesses (Product identifier, Product description, quantity sold, dollar value) [66].	Varies depending on store point of sale systems
v) Environment Scan: Level of influence of environmental-level enabling/impeding factors	Intervention and control stores (2022*, 2023, 2024) *2022 – Intervention only	Store owner/s (for privately owned stores), store representatives, or store nutritionists for stores with ALPA or Outback Stores (with or without store managers and/or area managers)	Environment scan: 26-item e-survey to collect data on the broader socio-ecological impacts on store practice. Survey informed by publicly available submissions to a Parliamentary Inquiry and the Good Food Planning Tool [67, 68]. Co-designed with stakeholders and built in REDCap	~ 15 min

#### Sample size

There are 53 eligible stores in 45 communities across the NT serviced by the partner s. We anticipate from previous trials an 85% consent rate and no withdrawals (or loss to follow up for the primary outcome). A sample of 36 communities will have 90% power to detect an ~ 3.5% lower percentage change in the primary outcome, free sugars g/MJ (SD of % change = 3%). The mean effect size of an ~ 3.5% reduction in free sugars (g/MJ) is based on our Healthy Stores 2020 trial [4]. We commenced recruitment in 2022 and recruited 32 stores (Fig. 1 and Additional Table 1).

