## Methods

This is a store-level pragmatic randomised parallel group, 2-arm, superiority trial with a 1:1 allocation. The study commenced in 2022.

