## Methods: assignment of interventions (for controlled trials)

### Allocation

Computer generated random numbers were used to allocate stores in near equal numbers to intervention/control within the store group serviced by each partner organisation (i.e., ALPA, NT Health (Central Australia), NT Health (Top-End), Katherine West, Miwatj, Outback Stores). Two stores with ALPA and two stores serviced by Miwatj were forced as each of these store pairs were in the same community and so 15 stores were allocated to intervention and 17 to control. Allocation occurred simultaneously after the required sample of stores was reached.

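### The sample size section asks for 36 communities, but 32 stores in at most 30 communities were recruited, and the article still says the required sample was reached

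*Protocol article*

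**What the plan says.** All statements are in the protocol article.

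- **Methods, opening paragraph:** a store-level, two-arm "superiority trial with a 1:1 allocation".
- **Sample size, eligible pool:** "There are 53 eligible stores in 45 communities across the NT". Stores and communities are thus counted separately.
- **Sample size, expectation:** "We anticipate from previous trials an 85% consent rate and no withdrawals".
- **Sample size, target:** "A sample of 36 communities will have 90% power to detect an" an approximately "3.5% lower percentage change in the primary outcome, free sugars g/MJ", with an SD of percentage change of 3%. No alpha or sidedness is given.
- **Sample size, outcome of recruitment:** "We commenced recruitment in 2022 and recruited 32 stores". The reader is referred to Fig. 1 and an additional table, neither of which is available here.
- **Allocation:** two ALPA stores formed a same-community pair, as did two Miwatj stores. The allocation of these pairs was forced, and the result was 15 intervention and 17 control stores. The section ends: "Allocation occurred simultaneously after the required sample of stores was reached".

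**The concern.** The only required sample in the article is 36 communities. The recruited number falls short of it in either unit: by 4 if each store is counted, and by at least 6 once the same-community pairs are counted as one community each. Yet the Allocation section reports that a requirement, now expressed in stores, was met. A reader cannot tell which requirement that was, whether the target had been lowered, or whether stores and communities were treated as interchangeable.

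The article reports recruitment and allocation in the past tense, so the achieved figures were available when it was written. The 90% power statement is what people will cite when they interpret the result, particularly a null one. As printed, it belongs to a sample of 36 communities that was not obtained, next to a sentence saying that recruitment was complete.

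**Working it through.** **Inputs.** Difference d = 3.5 and SD = 3 (both in percent change), power 90%, 1:1 allocation and no losses, all from the article. Alpha is assumed to be 5% two-sided.

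**Step 1. The plan's own figure.** Normal formula, per arm:

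n = 2 × (1.96 + 1.2816)² × (3/3.5)² = 15.4, so 16 per arm, 32 in total.

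With the noncentral t distribution, 16 per arm gives 89.1% and 17 per arm gives 91.0%, so 34 in total. The stated 36 (18 per arm) gives 93.8% (normal) or 92.5% (t). The 36 is therefore consistent with the inputs and carries a small margin. With 36, a difference of 3.34 has exactly 90% power (t), which fits the approximate sign on the 3.5%.

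**Step 2. The achieved number.** 32 stores, of which two pairs each share a community: 32 − 2 = 30 communities at most. Against 36, the shortfall is 36 − 32 = 4 counted as stores, or at least 36 − 30 = 6 counted as communities (6/36, about 17%).

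**Step 3. Power for the achieved sample.** SE = 3 × √(1/n₁ + 1/n₂); noncentrality = 3.5/SE. If each pair went to a single arm, 30 communities split 15/15, 14/16 or 13/17, depending on which arms the pairs were in.

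| Units | Split | SE | 3.5/SE | Power, normal | Power, t | Difference with 90% power (t) |
|---|---|---|---|---|---|---|
| 36 planned | 18/18 | 1.000 | 3.50 | 93.8% | 92.5% | 3.34% |
| 32 stores | 15/17 | 1.063 | 3.29 | 90.9% | 89.0% | 3.56% |
| 30 communities | 15/15 | 1.095 | 3.20 | 89.2% | 86.9% | 3.68% |
| 30 communities | 14/16 | 1.098 | 3.19 | 89.0% | 86.8% | 3.69% |
| 30 communities | 13/17 | 1.105 | 3.17 | 88.6% | 86.4% | 3.71% |

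Against the stated 90%, the loss is about 0 to 1 point counted as stores and about 1 to 4 points counted as communities.

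**Step 4. The planned ANCOVA.** The SD given is for percentage change, while the Analysis section plans ANCOVA on log-transformed outcomes with the baseline period. With equal variances at both times, the residual variance is (1 + r)/2 times the change-score variance, where r is the baseline to follow-up correlation. The article gives no r. Over an assumed range of 0.95 down to 0.8, with one degree of freedom lost, power (t) is 89.7% to 91.8% for 15/17 and 87.7% to 90.1% for 15/15.

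**The case against.** The strongest reply is that the shortfall hardly matters. The article's inputs need only 32 to 34 units, the trial is described as store-level, stores were allocated, and 32 stores give 89–91% power. ANCOVA may recover part of the rest. The 32 also stands in the same paragraph as the 36, so nothing is hidden. On power this reply largely stands: a reader might infer that the trial is materially underpowered, and the article's figures do not support that.

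It does not remove the inconsistency. The article chose communities for its target, distinguishes them from stores in the eligible pool, and treated same-community stores as linked when allocating. Even in stores, 32 is below 36, and no requirement of 32 stores is stated anywhere. The missing figure and additional table may give the exact community count, but they cannot make 32 stores into 36 communities.

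Three stronger readings should be resisted:

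- **Consent.** 32 of 53 stores is 60%, which might be read as failure of the 85% consent assumption. But this is recruited over eligible. The number invited is not given in the available text, so a consent rate cannot be calculated.
- **Much lower power.** Figures such as 64% or 34% arise only with a larger SD or a smaller effect than the article states. Most of the drop comes from those substituted assumptions, not from the shortfall.
- **Origin of the effect.** Whether 3.5%, taken from an earlier trial of a defined strategy, carries over to store-chosen actions is a matter of judgement. The source is openly stated and contradicts nothing in the text.

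**Conclusion.** The point holds as a reporting inconsistency. The stated target of 36 communities was missed by at least 6 communities (4 units if stores are counted), the unit changes without explanation, and the claim that the required sample was reached agrees with no target in the article.

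The consequence for power is small: roughly 0 to 4 points below 90%, with the difference detectable at 90% power (t) moving from about 3.3% at 36 units to about 3.6–3.7%. This rests on the article's difference and SD, on an assumed two-sided 5% level, and on 30 communities, which is an upper limit; fewer would lower the community-based figure. No correlation between stores within a community or store group has been added, because the article gives none. Any gain from ANCOVA is likewise unquantified, for want of a stated correlation.

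**What to change.** In Sample size, state that the target of 36 communities was not met and give the achieved sample in both units: 32 stores (15 intervention, 17 control) in at most 30 communities, replaced by the exact count from the trial's records. Say which unit the power calculation refers to.

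State alpha and sidedness, then restate power for that sample. With two-sided 5%, this is about 89–91% for 32 independent stores and about 86–89% for 30 communities, with 90% power (t) for a difference of about 3.6% to 3.7%. If the ANCOVA gain is to be claimed, give the correlation it relies on.

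In Allocation, correct the closing sentence, or explain which requirement was reached and when it was set.

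The cost is wording only. Recruitment, allocation and analysis do not change, and the quoted power becomes slightly less favourable.
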